### Study Population

A total sample size of 575 patients, 115 CP recipients and 460 matched controls (1:4 ratio), will be sufficient to detect a clinically important difference of 11.6% between two groups (CP recipients vs matched controls) in 30-day mortality using a two-tailed *z* test of proportions and chi-square test with 80% power and a 5% level of significance. This 11.6% difference represents a 12.4% mortality in the CP recipient group and 24.4% mortality in the matched control patients [23].

The treatment group (CP recipients group) will have 115 patients who have COVID-19 but have not recovered yet as per the inclusion criteria. The control group (comparator group) will have 460 patients who are either not consenting to receive CP or those who will not be able to receive CP due to nonavailability to compare the efficacy of the CP. Control group patients will be subjected to propensity score (PS) matching based on age, gender, diabetes mellitus (DM), hypertension (HTN), and intubation.

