### Statistical Analysis

Descriptive and inferential statistics will be used to characterize the study sample and test the hypotheses. Descriptive results for all quantitative variables such as age will be presented as mean (SD; for normally distributed data) or median with interquartile range (for data not normally distributed), while numbers (percentage) will be reported for all qualitative variables such as gender.

To assess the independent effect of CP transfusion safety and survival, we will conduct a PS-matching (based on age, gender, DM, HTN, and intubation) analysis. Among the predictors, exact matching will be enforced to achieve the balance for all predictors between the plasma and control groups.

The bivariate analysis will be performed using independent sample *t* test, Mann-Whitney *U* test, Pearson chi-square test, or Fisher exact test whenever appropriate to compare the demographic characteristics (eg, age, gender, nationality) and clinical characteristics (improvement in oxygenation, laboratory parameters, radiological findings, complications, and length of hospital stay) between those who will receive the CP and those who will not receive this therapy.

The multiple binary logistic regression model will be used to assess the effect of CP transfusion on 30-day mortality after adjusting for potential confounding factors compared to matched controls patients. The adjusted odds ratio and 95% confidence interval for the adjusted odds ratio will be reported. The Hosmer-Lemeshow goodness-of-fit statistics will be used to determine whether the model adequately describes the data.

The time-to-event analysis will be measured from the date of diagnosis. The overall survival at 30 days and 3 months will be evaluated using the Kaplan-Meier estimator and compared between the two groups (plasma recipients vs matched control patients) using the log-rank test. A Cox proportional hazard model will also be used to estimate the hazard ratio for in-hospital 30-day mortality for the plasma group compared with matched control group patients after adjusting for potential confounding factors. In addition, interactions between CP administration and all the predictors will be tested to see if the plasma effects will be the same in subgroups. A *P*<.05 (two-tailed) will be considered statistically significant. All statistical analyses will be performed using SPSS version 24 (IBM Corp).

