## Discussion

The study of the Saudi population at risk of severe COVID-19 has some distinct features, as Saudi Arabia was recently challenged by related coronaviruses including MERS-CoV that might lead to distinct immunological responses to SARS-CoV-2. The intention overriding the scientific merit of a randomized controlled trial during this pandemic is an attempt to add CP in the armamentarium against COVID-19, as this readily available agent has historically shown benefit in the treatment of related coronaviruses. There are multiple theoretical and scientific reasons to support our thinking that CP may turn out to be an effective treatment. However, the bottom line is that we do not have enough data to be certain. CP trials that have been published so far have limitations and conflicting data. Our group and others are working hard during this time to establish evidence that could support the therapeutic use of CP for patients with COVID-19.

Limitations of our study include, first, the design of the study, as we could not find it feasible to make the study a randomized controlled trial with our patient population due to the strong perceived benefit of CP in the minds of the patients and treating physicians in this situation. Second, our collaborating centers are of various levels from secondary to tertiary care hospitals with limitation of experience uniformity in conducting such a collaborative study. However, we intend to be a mutually supportive group and keep our study elements uniform. In addition, currently, anti–SARS-CoV-2 antibodies titration facilities are not available countrywide in Saudi Arabia. However, we plan to save aliquots of collected convalescent plasmas to test antibody titers whenever such facilities will be available. Last, we could not include the investigation of some biomarkers like interleukin-6 during treatment in our protocol, due to nonavailability in some centers. Nonetheless, treatment with CP seems promising to treat patients with COVID-19, and a national clinical trial to explore the efficacy and safety of CP is justified.

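### The named tests and the sample size ignore hospital; if plasma use differs between hospitals, P values will be too small and intervals too narrow

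*Protocol article*

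**What the plan says.** The Methods section calls the trial national and multicentre. The Discussion lists as a limitation that "our collaborating centers are of various levels from secondary to tertiary care hospitals". Under Study Population, controls are patients who refuse consent or "those who will not be able to receive CP due to nonavailability". The same section and Statistical Analysis both give the matching factors as age, gender, diabetes, hypertension and intubation. Hospital is not among them.

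Statistical Analysis then names the methods:
- t, Mann-Whitney, Pearson chi-square and Fisher tests for the bivariate comparisons, which include length of hospital stay;
- a log-rank test between the two groups, with no strata mentioned;
- a logistic model ("The multiple binary logistic regression model will be used to assess the effect of CP transfusion on 30-day mortality") and a Cox model, both adjusted for confounders that are not listed.

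ICU length of stay is a primary endpoint under Study Endpoint and Outcome Measures, but no regression model is named for any length-of-stay outcome. The size is given as "A total sample size of 575 patients, 115 CP recipients and 460 matched controls (1:4 ratio") "with 80% power and a 5% level of significance".

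**The concern.** The named tests take each patient as an independent observation. That fails if two things hold together: patients in one hospital share an outcome level, and the share receiving plasma differs between hospitals. The plasma comparison is then partly a comparison of hospitals, and there are far fewer hospitals than patients. The ordinary standard error does not see this.

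This is a matter of precision and arises even when a hospital's outcome level is unrelated to its plasma use. If the two are related, there is bias as well.

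What is at stake is the stated 5% level and the 95% confidence intervals. The interim analysis (40 recipients, 40 controls) uses a similar analysis, and Time of the Study makes an apparent benefit there the reason to enlarge and extend the trial.

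**Working it through.** **1. The plan's sample size.** With k = 4 controls per recipient and p̄ = (p1 + 4·p2)/5, the pooled formula is

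n = [1.96·√(1.25·p̄(1−p̄)) + 0.842·√(p1(1−p1) + p2(1−p2)/4)]² / (p1−p2)².

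- 12.8% versus 24.4% (difference 11.6 points): p̄ = 0.2208, n = (0.909 + 0.334)²/0.116² = 114.9. This gives 115 + 460 = 575, the plan's figure exactly.
- The printed pair, 12.4% versus 24.4%: 107 + 428 = 535. These rates differ by 12.0 points, not the stated 11.6. That is a separate matter.

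So 575 follows from independence, with no design effect.

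**2. When ignoring hospital matters.** Let m be patients per hospital, ρ the intraclass correlation of death within hospitals, and r the between-hospital correlation of plasma use (0 = no more variation in share than chance; 1 = each hospital treats all or none). With equal hospitals, and hospital effects unrelated to plasma use,

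true variance / ordinary variance ≈ 1 + (m−1)·ρ·r.

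Both ρ and r must be above zero for inflation. If the 1:4 ratio is held in every hospital, the ratio is 1−ρ and the ordinary test is slightly conservative.

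The formula agrees with simulation (no plasma effect, about 575 patients, 22% mortality, 8,000 runs per case, pooled two-proportion z test):

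| Assumed case | Formula for √(variance ratio) | Simulated SE ratio | Simulated two-sided error |
|---|---|---|---|
| Equal share, ρ = 0.10, 10 or 20 hospitals | √0.90 = 0.95 | 0.95 | 3.9% |
| 20 hospitals (m = 28), ρ = 0.05, r = 0.2 | √(1 + 27·0.05·0.2) = 1.13 | 1.13 | 8.3% |
| 10 hospitals (m = 57), ρ = 0.10, r = 0.2 | √(1 + 56·0.10·0.2) = 1.46 | 1.45 | 16.6% |

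With ρ from 0.01 to 0.10 and 10 or 20 hospitals, the error runs from 3.9% to 5.0% with an equal share and from 5.9% to 16.6% with r = 0.2. If every hospital treats all or none, it reaches 44.8%, but then nothing can be compared within a hospital.

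**3. The remedy tested.** Second model: normal hospital effects on the log-odds of death, beta-distributed plasma share with mean 0.2.

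| Assumed hospitals, SD of log-odds, r | Two-sided error, unadjusted test |
|---|---|
| 20, 0.5, equal share | 4.7% |
| 20, 0.5, 0.05 | 5.3% |
| 20, 0.5, 0.1 | 6.5% |
| 20, 0.5, 0.2 | 7.6% |
| 20, 0.5, 0.4 | 9.9% |
| 10, 0.7, 0.4 (every worst value) | about 20% |

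Repeated runs differ by up to about one percentage point. Over 10 to 30 hospitals, SD 0.3 to 0.7 and r 0.05 to 0.4, a Mantel-Haenszel test stratified by hospital stays at about 4% to 5.6%. A Mann-Whitney test on a stay-type outcome with an assumed intraclass correlation of 0.05 has error of about 5% to 17% over the same range.

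**The case against.** The strongest reply is that nothing in the article says plasma availability differs by hospital. Refusal is a patient's own choice. Availability could follow blood group or calendar time, and plasma can be frozen and shipped. The remark on centre levels goes on to concern uniformity of experience in running such a study, with an intention to keep its elements uniform, and says nothing about mortality. A reader might infer that the 5% level fails outright. The documents do not support that: with an equal plasma share the ordinary test is at or below 5%.

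A reader might also infer that every analysis ignores hospital. That is not supported either. The logistic and Cox covariates are unlisted and could include hospital, and an article may leave that list to the analysis plan, which is not shown. The simulations use an unadjusted, unmatched test, not the adjusted model.

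All of this stands, and it makes the point conditional. It does not remove it. The independent-sample tests, the log-rank test and the five matching factors are stated choices, not omitted detail. Nothing in them keeps the 1:4 ratio within a hospital, which is the case where ignoring hospital is harmless. Collecting, treating, storing and shipping plasma across centres of different levels makes uneven use a reasonable expectation.

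**Conclusion.** The point holds in conditional form. The named tests and the sample size treat patients as independent, and hospital is neither a matching factor nor a stated stratum. If plasma use differs between hospitals and outcomes do too, P values will be too small and intervals too narrow. On assumed inputs the unadjusted mortality test has a true error of about 5% with an equal plasma share, roughly 6% to 10% in middle cases and about 20% at the worst end of the range.

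These figures assume equal-sized hospitals and hospital effects unrelated to plasma use. The article gives no number of hospitals, intraclass correlation or plasma share, so no single figure can be claimed. The change is worth making because the stated tests depend on a balance that the plan does not secure, and a stratified test does not need it.

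**What to change.** In Statistical Analysis, state that:
- the group comparisons of ICU stay and mortality are stratified by hospital (Mantel-Haenszel, stratified rank and stratified log-rank tests);
- hospital enters the logistic model as a stratum or random intercept, and the Cox model as a stratum or frailty;
- a within-hospital comparison is a sensitivity analysis;
- the interim analysis follows the same rules.

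Do not rely on clustered standard errors alone. They leave any bias from hospital in the estimate and are unreliable with few hospitals.

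The cost is wording, since hospital should be known for every patient from the hospital records. Hospitals with only recipients or only controls add nothing to the stratified comparison. In the model above, stratifying multiplies the ordinary standard error by about √((1−ρ)/(1−r)). With 20 hospitals and SD 0.5, ρ ≈ 0.22·0.78·0.5² = 0.043, so the factor is √(0.957/0.8) = 1.09 at r = 0.2 and √(0.957/0.6) = 1.26 at r = 0.4. The true standard error of the unstratified test, with m = 29, is already √(1 + 28·0.043·0.2) = 1.11 and √(1 + 28·0.043·0.4) = 1.22 times the ordinary one. Against a correct unstratified interval, then, little precision is lost.

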### Transfusion of CP for Treatment of COVID-19

After obtaining informed consent, eligible patients who have severe COVID-19 and have not recovered yet will be infused with the donated CP 300 ml (200-400 ml/treatment dose) at least once and, if needed, daily for up to 5 sessions (Figure 3).

Other supportive and therapeutic measures should continue according to the locally approved protocols with due diligence. Patients will be monitored after FFP transfusion for the usual side effects of blood product transfusion (eg, allergic or febrile reactions, TRALI, and circulatory overload). We will then assess the response after the infusion of the plasma in these patients as detailed in the Response Assessment section.

As with other plasma therapies, attention should be given to ABO compatibility. For plasma selection, we will consider ABO compatibility (Table 2) regardless of Rh status. To minimize the risk of TRALI, preference will be given to plasma from male donors and nulliparous women.

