### Data Collection

Clinical information of all enrolled patients will be retrieved from the hospital electronic or paper records system, including the following:

Baseline demographic dataDays of illness durationPresenting symptomsRadiological findings (chest x-ray and computed tomography [CT] scan chest, if possible) on the day of hospital admission; on the day of ICU admission; on the day of CP infusion (day 0); and on days 3, 7, 14, and 30Laboratory infectious marker testing results like respiratory, urinary, or blood cultureLaboratory inflammatory markers: CRP (day of CP infusion [day 0] and then on days 3, 7, 14, and 30)Application of assisted mechanical ventilation and their modes, intranasal oxygen inhalation, number of days of intubation, or nasal oxygen supportMedication regimen (eg, hydroxychloroquine, azithromycin, any antiviral therapies, steroids, tocilizumab)Complications including acute renal failure, acute coronary syndrome, myocarditis, ARDS, gastrointestinal complication, and nosocomial infectionThe SARS-CoV-2 RNA from the serum sample will be monitored during treatment and at day 14 of recovery or discharge, whichever is later.

We plan to test for all of the following parameters for patients with COVID-19:

Complete blood count (CBC) differential to include percent and ALC, and percent and absolute neutrophil countChemistry panel to include total protein, albumin, lactate dehydrogenase, alanine aminotransferase and aspartate aminotransferase, and procalcitoninCardiac biomarkers (eg, cardiac troponins)Creatine phosphokinaseFerritinFull coagulation profile to include partial thromboplastin (PT), activated PT time, fibrinogen, and D-dimerCRPOxygen saturationRadiological examinationABO RhD grouping and antibody screeningrRT-PCR test for SARS-CoV-2Test for IgG and IgM antibodies against SARS-CoV-2

CP donors will essentially undergo routine blood donation processes such as donor history questionnaire, clinical examination, and testing for the infectious marker (serology and nucleic acid testing methods) along with ABO RhD grouping, antibody screening, and CBC. They will also undergo a test for IgG and IgM antibodies against SARS-CoV-2, which should be positive for IgG.

Data collection forms have been developed to collect data for CP donors, recipients, and controls (comparators).

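### Survival is timed from diagnosis, but groups are defined by a later infusion and controls have no index day, so recipients' guaranteed survival before infusion is credited to plasma

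*Protocol article*

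**What the plan says.** **Time origin and comparison (Statistical Analysis).** "The time-to-event analysis will be measured from the date of diagnosis." The next sentence reads "The overall survival at 30 days and 3 months will be evaluated using the Kaplan-Meier estimator and compared between the two groups". A Cox model is then to "estimate the hazard ratio for in-hospital 30-day mortality for the plasma group compared with matched control group patients".

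**When plasma is given.** Recipients need a positive PCR and ICU-level, severe or life-threatening disease (Inclusion Criteria). The article goes on: "After obtaining informed consent, eligible patients who have severe COVID-19 and have not recovered yet will be infused with the donated CP" (section Transfusion of CP for Treatment of COVID-19). A recipient is therefore alive and still ill at infusion.

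**Who the controls are (Study Population).** They are patients "either not consenting to receive CP or those who will not be able to receive CP due to nonavailability". They undergo "propensity score (PS) matching based on age, gender, diabetes mellitus (DM), hypertension (HTN), and intubation".

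**Index day (Data Collection).** Radiology is scheduled "on the day of CP infusion (day 0") and on fixed days after that, and CRP follows the same day 0. No corresponding day is given for controls. Duration of illness is collected but is not a matching variable.

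The article mentions no time-dependent exposure, landmark, delayed entry or matching on elapsed time.

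**The concern.** Group membership depends on an event that happens after the clock starts. A patient counts as a recipient only by living until infusion, so the interval before infusion contributes follow-up but no deaths to the plasma group. Nothing equivalent applies to a control. The result is immortal-time bias, which lowers the plasma group's apparent death rate even if plasma does nothing.

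Two things raise the stakes. First, 30-day mortality is a secondary endpoint, but the sample size rests on it. Second, the interim look at 40 recipients and 40 controls uses a similar analysis, and an apparent benefit there leads to a larger sample and a longer trial (Time of the Study; Interim Analysis). Without randomization, a sound time origin is one of the few protections available.

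The article states the origin expressly, so this is not a detail left to a fuller analysis plan.

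**Working it through.** **1. The plan's own figure.** A pooled two-sided z test at 5%, 80% power and 1:4 allocation, with 12.8% against 24.4% (the stated 11.6-point difference), gives exactly 115 + 460 = 575, with power 80.1%. The printed 12.4% against 24.4% is a 12.0-point difference and gives 107 + 428 = 535. That mismatch is a separate matter. Only the 24.4% is needed below.

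**2. Inputs.** Control 30-day mortality is 24.4% (Study Population), taken here as measured from diagnosis. True plasma effect is zero. The differential delay *w*, meaning days of guaranteed survival that recipients have and controls do not, is assumed to be 1 to 10 days because the article gives none.

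**3. Constant hazard.** *h* = −ln(1 − 0.244)/30 = 0.2797/30 = 0.00932 per day.

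- Recipient mortality by day 30: *p* = 1 − exp(−*h*(30 − *w*)).
- Recipient person-days: *w* + *p*/*h*.
- Rate ratio under no effect: (*p*/*h*) / (*w* + *p*/*h*).

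Example, *w* = 5: *p* = 1 − exp(−0.00932 × 25) = 20.8%. The gap is 24.4 − 20.8 = 3.6 points. The rate ratio is 22.3/(5 + 22.3) = 0.82.

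**4. Other hazard shapes.** With a Weibull cumulative hazard *H*(t) = 0.2797 × (t/30)^k, recipient mortality is 1 − exp(−(*H*(30) − *H*(*w*))). Shape 1.5 means hazard rises over time; shape 0.7 means deaths come early.

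| Delay *w* (days) | Recipient mortality, constant hazard | Gap (points) | Rate ratio | Gap, shape 1.5 | Gap, shape 0.7 |
|---|---|---|---|---|---|
| 1 | 23.7% | 0.7 | 0.96 | 0.1 | 2.0 |
| 3 | 22.3% | 2.1 | 0.89 | 0.7 | 4.3 |
| 5 | 20.8% | 3.6 | 0.82 | 1.5 | 6.3 |
| 7 | 19.3% | 5.1 | 0.75 | 2.4 | 8.0 |
| 10 | 17.0% | 7.4 | 0.65 | 4.2 | 10.5 |

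**5. The Cox model itself.** A simulation with 115 recipients, 460 controls, no plasma effect, constant hazard and exponentially distributed delays (1,000 runs per setting, no covariates) gave:

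| Mean delay (days) | Hazard ratio, clock from diagnosis | Significant in favour of plasma (nominal 2.5%) |
|---|---|---|
| 1 | 0.94 | 2.7% |
| 3 | 0.87 | 6.6% |
| 5 | 0.81 | 13.0% |
| 7 | 0.74 | 22.3% |
| 10 | 0.65 | 39.7% |

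When recipients entered the risk set only at infusion, the hazard ratio returned to 0.98–0.99 and the false-positive rate to about 1–2%. The time origin alone produces the distortion.

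**The case against.** The strongest objection is that much of the time from diagnosis to infusion may be shared. If controls, like recipients, must have reached ICU-level or severe disease, both groups are guaranteed survival to that point. Only the wait from eligibility to infusion then differs. This stands: a wait of 1 to 3 days gives 0.7 to 2.1 points under constant hazard. It reduces the bias but does not change its direction, and the article sets no limit on the wait. Hazard shape is also unknown, and a rising hazard shrinks the gap considerably.

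A reader might infer more than the text supports:

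- *That a consenting patient who dies while waiting becomes a control by definition.* Study Population does not say how such a patient is classified, and exclusion is possible. The bias does not need this step.
- *That the trial will show a false benefit.* Only this component points that way. Allocation is non-random, and unmatched severity could offset or reverse it.
- *That every mortality analysis is affected.* The quoted sentence governs the time-to-event analysis. The logistic model and the chi-square comparison have no stated origin and share the problem only if theirs is also diagnosis. For the same reason, the planned 11.6 points is only a yardstick.
- *That ICU stay is biased in the opposite direction.* This does not follow from the quoted sentence, and the article gives nothing from which to quantify it.
- *That day 0 in Data Collection contradicts the survival origin.* It is a measurement schedule. It shows that controls lack an index day, not that two survival clocks conflict.

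**Conclusion.** The point holds for Kaplan-Meier, log-rank and Cox. As written, these analyses give recipients guaranteed survival from diagnosis to infusion that controls do not have, and matching on age, gender, diabetes, hypertension and intubation cannot remove it. This component favours plasma.

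Its size cannot be read from the article. With no true effect, constant hazard and 24.4% control mortality, differential delays of 1, 3, 5, 7 and 10 days give spurious gaps of about 0.7, 2.1, 3.6, 5.1 and 7.4 points. At 5 to 10 days the gap is about 1.5–4.2 points if hazard rises over time and 6.3–10.5 if deaths are early. The effect is minor if the differential wait is about a day and serious if it approaches a week. The sentence should be changed because nothing in the plan keeps the wait short or adjusts for it.

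**What to change.** Replace the sentence on the time origin under Statistical Analysis with one of two rules.

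1. **Time-dependent exposure.** Keep the existing cohort. In the Cox model, count a recipient as untreated until first infusion and treated from then on, or let recipients enter the risk set at infusion. Kaplan-Meier curves and log-rank tests by eventual group, started at diagnosis, would still carry the bias and should be dropped or restarted from an index day.
2. **Matched index day.** Start follow-up at first infusion for recipients. Give each control the same elapsed time since ICU admission or diagnosis as its matched recipient, and require the control to be alive, in hospital, eligible and untransfused on that day. Take intubation status on that day, and use the same origin for 30-day mortality.

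Cost: no change to treatment. The second rule requires each control's status on the index day to be abstracted from records. Some controls will leave the pool, so with exact matching on five variables the full 1:4 ratio may not be reached. The time-dependent Cox option avoids that loss.

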### Study Endpoint and Outcome Measures

Our primary endpoints are ICU (or designated area for critical patients) length of stay; safety of CP; and reporting of SAE such as anaphylaxis, TRALI, and TACO.

Our secondary endpoints will include number of days on mechanical ventilation, 30-day mortality, and days to clinical recovery as defined by the MOH.

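### The Cox model alone is restricted to in-hospital deaths, so its adjusted hazard ratio does not estimate the effect on the stated 30-day mortality endpoint (minor)

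*Protocol article*

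**What the plan says.** All of these statements are in the Protocol article.

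- **Study Endpoint and Outcome Measures.** The secondary endpoints are "number of days on mechanical ventilation, 30-day mortality, and days to clinical recovery as defined by the MOH". Mortality is not limited to hospital.
- **Study Population.** The trial is sized on 30-day mortality, with "12.4% mortality in the CP recipient group and 24.4% mortality in the matched control patients". There is again no limit to hospital.
- **Statistical Analysis, logistic model.** It is to "assess the effect of CP transfusion on 30-day mortality after adjusting for potential confounding factors".
- **Statistical Analysis, survival curves.** "The overall survival at 30 days and 3 months will be evaluated using the Kaplan-Meier estimator", with a log-rank comparison of the two groups.
- **Statistical Analysis, Cox model.** In the sentence that follows, the Cox model is to "estimate the hazard ratio for in-hospital 30-day mortality for the plasma group compared with matched control group patients".

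The time origin is common to the survival analyses: "The time-to-event analysis will be measured from the date of diagnosis". What separates the Cox model from the others is therefore the event, not the clock. In-hospital death is not listed as an endpoint, and no reason is given for using it here.

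**The concern.** The log-rank test and the adjusted hazard ratio would normally be read together as one survival result, and the hazard ratio would be read beside the adjusted odds ratio. Here the hazard ratio counts a narrower event than either. A patient discharged alive on day 12 who dies on day 25 is a death for the endpoint, the logistic model and the Kaplan-Meier curve, but not for the Cox model.

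An event limited to hospital also makes the estimate depend on when patients leave. Unequal discharge is plausible under the trial's own hypothesis: the Abstract says the study is to detect a difference in hospital stay, and "Our primary endpoints are ICU (or designated area for critical patients) length of stay". At stake is whether the adjusted hazard ratio can be reported as an effect on 30-day mortality. The Interim Analysis section plans a similar analysis of the first 40 CP recipients and 40 controls, so the wording carries over to that look as well.

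**Working it through.** **1. What the sample size refers to.** With a 1:4 ratio, two-sided 5%, 80% power, control mortality 24.4% and a "clinically important difference of 11.6% between two groups", CP mortality is 24.4 − 11.6 = 12.8%. The pooled rate is (0.128 + 4 × 0.244)/5 = 0.2208.

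n(CP) = [1.96 × √(0.2208 × 0.7792 × 1.25) + 0.8416 × √(0.128 × 0.872 + 0.244 × 0.756/4)]² / 0.116² = [0.909 + 0.334]² / 0.01346 ≈ 114.9, so 115.

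Controls are 4 × 115 = 460, total 575. The plan's figure is reproduced, and it is a figure for 30-day mortality compared as proportions. It does not depend on the Cox model. (The two printed rates differ by 12.0 points, not 11.6. That is a separate matter.)

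**2. The events side by side.**

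| Element | Event counted | Death after discharge, before day 30 |
|---|---|---|
| Secondary endpoint | 30-day mortality | counted |
| Sample size | 30-day mortality | counted |
| Logistic model | 30-day mortality | counted |
| Kaplan-Meier, log-rank | overall survival, 30 days and 3 months | counted |
| Cox model | in-hospital 30-day mortality | not counted |

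**3. What the Cox model estimates under each handling of discharge.** Let d be the daily hazard of death in hospital and m the daily hazard of discharge alive.

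- *Censored at discharge:* the hazard ratio is d(CP)/d(control), a cause-specific ratio that does not involve m.
- *Kept at risk to day 30:* the hazard ratio reflects the cumulative in-hospital deaths, which depend on d and m, and deaths after discharge are missed.
- *All deaths to day 30:* this is the stated endpoint. It depends on d, m and the hazard after discharge.

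**4. Illustration on assumed hazards.** None of these hazards is in the article. Assume d = 0.012 per day in both groups, control m = 0.04 per day, and death after discharge at 0.001 per day. Cox models fitted to simulated data (80,000 controls, 20,000 CP) gave:

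| CP discharge per day | HR, all 30-day deaths | HR, in-hospital, censored at discharge | HR, in-hospital, kept to day 30 |
|---|---|---|---|
| 0.04 (equal) | 0.97 | 0.98 | 0.97 |
| 0.08 (doubled) | 0.73 | 1.02 | 0.67 |
| 0.03 (slower) | 1.14 | 1.02 | 1.15 |

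In the first row all three values are 1.00 in theory, as is the censored ratio in every row, so simulation error is about 0.03. Solving the large-sample Cox equation for the same hazards gives 0.70, 1.00 and 0.66 for the second row and 1.11, 1.00 and 1.13 for the third.

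**5. A milder case.** Choose d so that d/(d + m) × [1 − exp(−30(d + m))] = 0.244 at m = 0.04. This gives d ≈ 0.017. Let CP discharge be 30% faster or slower, with the same d in both groups.

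- With no deaths after discharge, the kept-at-risk ratio equals the all-deaths ratio: 0.87 (faster) and 1.16 (slower).
- With 0.0005 to 0.002 deaths per day after discharge, the all-deaths ratio is 0.88 to 0.90 (faster) or 1.13 to 1.15 (slower), against 0.87 and 1.16. The gap is at most about 0.03.
- Censoring at discharge gives 1.00 throughout.

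The gap therefore ranges from nothing to substantial, depending on two quantities that the article does not give and on how discharge is handled.

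**The case against.** The strongest reply is that this is one word in one supplementary analysis. The trial is sized on a test of proportions, mortality is a secondary endpoint, and the logistic model and the log-rank test already address 30-day death without the restriction. Rules for discharge are commonly left to the full protocol or analysis plan, so their absence from an article is no fault. All of this stands, and it is why the point is minor. It does not remove the mismatch, because the event definition is printed and not left open.

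A reader might go further and infer that discharge must distort the hazard ratio, so that the Cox result will be wrong however discharge is handled. The documents do not support that. Censoring at discharge gives a valid cause-specific ratio for in-hospital death, which answers another question. Keeping patients at risk gives almost the 30-day mortality ratio when few deaths follow discharge. With equal discharge rates all three ratios can agree.

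Nor is a gap between hazard ratio and odds ratio evidence of a discharge effect. At the printed rates the odds ratio is (0.124/0.876)/(0.244/0.756) = 0.44, and the proportional-hazards ratio is ln(0.876)/ln(0.756) = 0.47, with no discharge involved.

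**Conclusion.** The concern holds as an inconsistency in the event definition. The Cox model as worded excludes deaths after discharge, so its adjusted hazard ratio does not estimate the effect on the 30-day mortality endpoint that the rest of the plan uses.

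Its numerical size and direction cannot be derived from the article. They depend on whether the groups leave hospital at different rates, on how many patients die after discharge, and on how discharge is handled. The hazard ratios in the working are illustrations on assumed constant hazards, not predictions for this trial. The sample size and the other mortality analyses are unaffected. Severity is minor.

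**What to change.** In Statistical Analysis, delete *in-hospital* from the Cox sentence, so that the model uses death from any cause, in any place, within 30 days, as the other mortality analyses do. State that patients discharged alive stay at risk to day 30 and are not censored at discharge. If in-hospital death is of interest, report it as a separate, named outcome with discharge alive as a competing event.

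The cost is one wording change and a day-30 vital-status check, in both groups, for patients discharged earlier. Much of that work is already implied, since survival at 3 months cannot be estimated without vital status after discharge.
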